### Statistical analysis

#### Sample size justification

Based on our observational studies and findings from recent dose evaluation studies on healthy children, we estimate that no more than 40 % of the usual care arm will have postoperative 25OHD levels above 50 nmol/L. Based on the 25OHD levels achieved with 1600 IU/day in recent studies on approximate IOM high dose in healthy children, we anticipate that 80 % of the high dose arm will have postoperative levels above 50 nmol/L. Therefore group sample sizes of 28 in both treatment arms will be required to achieve 80 % power to detect an absolute difference between the group proportions of 0.40. The test statistic used is the two-sided Fisher’s exact test and the significance level of the test was targeted at 0.05. Assuming a 10 % drop-out rate, approximately 62 patients (total) will need to be recruited.

#### Comments on power for evaluating vitamin D-related adverse outcomes

**Hypercalcemia** - Our previous observational study (n = 58) identified no cases of preoperative or immediate postoperative hypercalcemia [26]. With a baseline rate in the usual care arm between 0 and 10 %, our sample size would be sufficient to show a statistically significant absolute difference between groups if the rate in the high dose arm exceeded 30 %.

**Hypercalciuria** - Information on baseline rates of hypercalciuria prior to or following cardiac surgery with usual care vitamin D intake is not available. The proposed sample size would be sufficient to demonstrate a 35 % absolute difference in proportions if the baseline pre- or postoperative rates are up to 20 %.

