#### Vitamin D-related adverse events

We will report, by intervention, on the occurrence of clinically significant adverse events. However, a measurable difference in clinically significant adverse events between the high dose and usual care arms of the study is unlikely. Therefore, to enhance our ability to evaluate for potential toxicity, we will use two well-accepted surrogate outcome measures:*Hypercalcemia:* This will be defined as an ionized calcium level above 1.40 mmol/L (or above 1.45 mmol/L for children under 8 weeks) (Table 3). We will evaluate for hypercalcemia in blood collected immediately before surgery and throughout the postoperative course (measurements are a standard of care, and any single episode of hypercalcemia not related to parenteral administration of calcium will be considered an adverse event) [64].

**Table 3 Tab3:** Safety thresholds for ionized calcium, total corrected calcium and elevated calcium-creatinine ratio

Table 3A: Age specific thresholds for pH corrected ionized calcium levels	
Age (months)	95th % (mmol/L)
<2	1.45
>2	1.4
Table 3B: Threshold for corrected total calcium level	
Age (months)	mmol/L
<3	2.8
>3	2.7
Table 3C: Age specific thresholds for elevated calcium-creatinine ratio	
Age (year)	95th % Ca/Cr ratio (mmol/mmol)
<1	2.2
1–2	1.5
2–3	1.4
3–5	1.1
5–7	0.8
7–17	0.7*Hypercalciuria -* We will identify hypercalciuria using calcium:creatinine ratios defined using age-specific norms and thresholds (Table 3) [64–66]. Measurements will be performed on urine collected in the operating room immediately prior to surgery and on the first postoperative day.

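### The hypercalcemia power statement fails over most of its own 0–10% baseline range: at a 10% usual-care rate, power for a 30% high-dose rate is 33–39%

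*Protocol article*

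**What the plan says.** In the Protocol article, 'Comments on power for evaluating vitamin D-related adverse outcomes', the hypercalcemia paragraph first reports that the group's earlier observational study of 58 children "identified no cases of preoperative or immediate postoperative hypercalcemia". It then sets a range for the control arm: "With a baseline rate in the usual care arm between 0 and 10"%. For that whole range it makes the claim that "our sample size would be sufficient to show a statistically significant absolute difference between groups if the rate in the high dose arm exceeded" a single threshold, which is 30%. It states neither a power level nor a test.

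'Sample size justification' supplies the only design parameters. Power is set at 80% for a difference in proportions of 0.40, and the arm size follows: "group sample sizes of 28 in both treatment arms will be required to achieve" it. The test is named as well: "The test statistic used is the two-sided Fisher’s exact test and the significance level of the test was targeted at 0.05". Recruitment is inflated to 62 in total for 10% drop-out. 'Secondary outcomes' allows either Fisher's exact or chi-square for hypercalcemia.

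The outcome itself is defined under 'Vitamin D-related adverse events'. Ionized calcium is assessed just before surgery and throughout the postoperative course, and "any single episode of hypercalcemia not related to parenteral administration of calcium will be considered an adverse event".

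**The concern.** The sentence covers every usual-care rate from 0 to 10%. With a fixed number of children, the difference that can be detected depends strongly on the control rate, so one 30% threshold is unlikely to suit both ends of that range. Moving the control rate from 0 to 10% cuts the true difference from 30 to 20 percentage points and adds variability in the control arm.

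The stake is interpretation. Vitamin D-related adverse events are the first secondary objective. The article says that a measurable difference in clinically significant events is unlikely, and it adopts hypercalcemia as one of two surrogates for toxicity for that reason. If readers believe that a 30% rate would have been detected, they may take p > 0.05 as reassurance about the high dose when a larger trial is planned.

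**Working it through.** **Inputs.** Usual-care rate p1 from 0 to 10% and high-dose rate p2 = 30% (comments on power). n = 28 per arm evaluable, or 62/2 = 31 per arm with no drop-out (sample size justification). Two-sided Fisher's exact test, alpha 0.05 (same section). The 80% power level is carried over from the primary outcome, which is an assumption.

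**Formula.** Exact power = Σx Σy b(x; n, p1) · b(y; n, p2) · 1[p(x, y) < 0.05]. Here b is the binomial probability, and p(x, y) is the two-sided p value for x/n events under usual care and y/n under high dose.

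**Calibration on the plan's own figure.** For the primary outcome, 40% v 80% with n = 28 gives Fisher power of 82.3%. The stated 28 per arm for 80% power is therefore sound, and the same method is a fair yardstick for hypercalcemia.

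**Lower end of the range, in detail.** With p1 = 0 the control count is always 0. Then 0/28 v 5/28 gives p = 2·C(28,5)/C(56,5) = 2 × 98,280 / 3,819,816 = 0.051. And 0/28 v 6/28 gives p = 2·C(28,6)/C(56,6) = 2 × 376,740 / 32,468,436 = 0.023. Six events are needed, and P(Y ≥ 6 | 28, 0.30) = 0.887. The statement holds here.

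**Upper end.** With p1 = 10% the expected counts are 2.8 v 8.4. The smallest significant high-dose count is 6 against 0 control events, 8 against 1, 9 against 2 and 11 against 3. The expected high-dose count falls short of what the typical control count demands.

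**Power for a 30% high-dose rate, 28 (31) per arm:**

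| Usual-care rate | Fisher, two-sided | Chi-square, uncorrected |
|---|---|---|
| 0% | 89% (94%) | 98% (99%) |
| 1% | 82% (88%) | 95% (97%) |
| 2% | 76% (83%) | 91% (94%) |
| 5% | 58% (66%) | 75% (79%) |
| 7.5% | 45% (52%) | 60% (65%) |
| 10% | 33% (39%) | 47% (52%) |

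**What a 10% usual-care rate would require.** By Fisher's test with 28 per arm, power is 79.4% at a 45% high-dose rate and 80.6% at 45.5%, so about 46% is needed. With 31 per arm it is 80.5% at 43%. By chi-square the figures are about 42% and 40%. Conversely, 10% v 30% at 80% power needs about 62 per arm by the normal approximation, or 72 with continuity correction.

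**How far the earlier data support the range.** The exact two-sided 95% upper limit for 0/58 is 1 − 0.025^(1/58) = 6.2%. So even for the samples it covers, the earlier study does not exclude baselines at which Fisher power is below 60%. It covers only preoperative and immediate postoperative samples, whereas the trial counts any qualifying episode throughout the postoperative course. The control rate for the trial's own outcome is therefore uncertain.

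**The case against.** **No power level is stated.** The sentence could describe observed rates that reach p < 0.05. On that reading it does better. A reader might infer that even an observed result of about 10% v 30% would not be significant, but the figures do not support this in general. With 28 per arm, the largest control count within 0–10% is 2 (7.1%) and the smallest high-dose count above 30% is 9 (32.1%). For 2/28 v 9/28, Fisher p = 0.040 and chi-square p = 0.019. The pairing 3/28 v 9/28 (Fisher p = 0.10) is no counter-example, because 3/28 is 10.7%. With 31 per arm, 3/31 v 10/31 fails by Fisher (p = 0.059) and passes by chi-square (p = 0.029). The objection stands against that stronger claim. It does not rescue the sentence as a statement about power, which is how a section headed as comments on power will be read.

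**Chi-square is permitted.** It extends the baseline range with 80% power to about 4% with 28 per arm (just under 5% with 31). The limit of about 1% is therefore specific to Fisher's test with 28 per arm. At 10%, chi-square still gives only 47% (52%).

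**Perhaps a 30-point difference was meant.** For 10% v 40%, power is 66% (73%) by Fisher and 76% (81%) by chi-square. But the text refers to the rate in the high-dose arm, while the neighbouring hypercalciuria sentence refers to an absolute difference.

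**The true baseline may be near zero.** The only data in the document are 0/58, where power is best. A reader might infer instead that counting every episode pushes the control rate above 10%. The document gives no rate for that outcome. Serial calcium values in one child are not independent, and episodes related to parenteral calcium are excluded. Uncertain is as far as the evidence goes.

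**Little depends on the sentence.** It sets no sample size and triggers no rule. Individual safety rests on measured thresholds and board review. This stands, and it limits the weight of the point.

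**Conclusion.** The statement is wrong as written for most of its own range. At 80% power with two-sided Fisher's exact test at 0.05, it holds only up to a usual-care rate of about 1% with 28 per arm, or about 2% with 31. At 10%, a true 30% high-dose rate would be missed about two times in three by Fisher's test and about half the time by chi-square. The conclusion rests on reading the sentence as a power claim and on carrying over the 80% level. The failure at 10% does not depend on which permitted test is used; the exact point along the range where power drops below 80% does.

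This is a modest correction to a comment on a secondary safety outcome. It does not call the sample size or the primary analysis into question. Nor does the article itself claim that a non-significant comparison would show safety; the risk is that readers draw that inference.

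**What to change.** Replace the sentence with one that states the test, the power and the dependence on baseline. For example: With 28 per arm and two-sided Fisher's exact test at 0.05, there is about 80% power for a 30% high-dose rate only if the usual-care rate is about 1% or less; at a 10% usual-care rate, 80% power needs a high-dose rate of about 46% (about 43% with 31 per arm).

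Add that hypercalcemia will be reported as arm-specific rates and their difference with exact 95% confidence intervals, and that a non-significant result does not show safety. Note also that the 0/58 figure covers only preoperative and immediate postoperative samples, so the usual-care rate for the trial's outcome is uncertain.

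Leave the definition of hypercalcemia as it is; correcting the power sentence does not require narrowing a prespecified safety outcome. The cost is a few sentences and a less favourable stated figure. Enrolment, data collection and the primary analysis are unaffected.

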#### Statistical procedures

The analyses will be conducted using SAS software (Copyright SAS Institute Inc., Cary, NC, USA) and a *P* value less than 0.05 will be considered statistically significant.

#### Descriptive statistics

Treatment groups will be described and compared using (i) means with standard deviations or medians with inter-quartile range values for continuous variables or (ii) frequencies with percentages for categorical variables. Statistically significant differences will be determined using Chi-square and Fisher’s exact tests for categorical variables, and t-tests or nonparametric tests (for example, Wilcoxon) for continuous variables, as appropriate.

#### Primary outcome

The primary analytical approach will be to evaluate all randomized patients in an intention to treat analysis. Differences in the primary outcome measure, proportion with 25OHD <50 nmol/L, between the treatment groups will be evaluated using the Fisher’s exact test. Logistic regression analysis will be used if important variables are unevenly distributed between groups. We anticipate minimal missing data because more than 95 % of participants from the recently completed observational study had an immediate postoperative sample [26].

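### Fisher's exact test for the primary outcome is valid and adequately powered but conservative; naming Boschloo's test before unblinding would add power at the same 0.05 for almost no cost

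*Protocol article*

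**What the plan says.** In the protocol article, Sample size justification states: "The test statistic used is the two-sided Fisher’s exact test", and "the significance level of the test was targeted at 0.05". It assumes that "no more than 40 % of the usual care arm will have postoperative 25OHD levels above 50 nmol/L" and that "80 % of the high dose arm will have postoperative levels above 50 nmol/L". From this it concludes that "group sample sizes of 28 in both treatment arms will be required to achieve 80 % power". It then adds: "Assuming a 10 % drop-out rate, approximately 62 patients (total) will need to be recruited".

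Primary outcome says that the plan will "evaluate all randomized patients in an intention to treat analysis" and that the difference in the proportion deficient "will be evaluated using the Fisher’s exact test". Sizing and analysis therefore name the same test. The article makes no claim about the error rate that the test actually attains.

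Secondary outcomes allows either Fisher's exact test or chi-square for hypercalcemia and hypercalciuria.

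**The concern.** Fisher's test conditions on the total number of deficient children. The design fixes the number randomized but not that total. With arms of about 30, few tables are possible for any given total, so the test usually cannot come close to 0.05 and stops well below it. The unused error rate is unused power. In a trial of 62 children, a real reduction in deficiency could be reported as not significant when another exact test, with the same error guarantee, would have declared it.

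Boschloo's test uses the Fisher P value only to rank the tables. It then sets the cut-off so that the rejection probability, maximized over every possible common proportion, stays at or below 0.05. Its rejection region contains Fisher's, so no Fisher-significant result is lost.

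**Working it through.** **Inputs.** From Sample size justification: two-sided 0.05, 28 per arm, proportions above 50 nmol/L of 0.40 (usual care) and 0.80 (high dose), 10% drop-out, 62 in total. From Primary outcome: all randomized patients analysed, samples expected in more than 95%, so about 59 (0.95 × 62 = 58.9) to 62 children. Assumption: the two-sided Fisher P value is the usual one, the summed probability of all tables no more likely than the one observed.

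**Formulas.** With X ~ Bin(n₁, p₁), Y ~ Bin(n₂, p₂) and rejection region R:

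- power = Σ over (x, y) in R of P(X = x) P(Y = y)
- maximum error = the largest value of that sum over a common p₁ = p₂ = p in (0, 1)
- Fisher: R = tables with Fisher P ≤ 0.05
- Boschloo: R = tables with Fisher P ≤ c, with c the largest cut-off that keeps the maximum error at or below 0.05

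**Step 1: the plan's own figure.** Fisher power at 0.40 versus 0.80 is 0.799 at 26 per arm, 0.802 at 27 and 0.823 at 28. The stated 80% at 28 per arm holds. For drop-out, 56 × 1.1 = 61.6, or 62. The stated figures reproduce.

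**Step 2: error and power by analysed split, 40% versus 80%.**

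| Usual care / high dose | Fisher max. error | Boschloo max. error | Power, Fisher → Boschloo | Gain (points) |
|---|---|---|---|---|
| 28/28 | 2.8% | 4.6% | 82.3% → 87.3% | 5.0 |
| 29/29 | 2.5% | 4.8% | 83.0% → 89.0% | 6.0 |
| 30/30 | 2.7% | 4.7% | 85.1% → 89.9% | 4.9 |
| 31/31 | 3.0% | 4.8% | 87.0% → 91.3% | 4.3 |
| 28/27 | 3.8% | 4.7% | 84.1% → 86.9% | 2.8 |
| 29/28 | 3.4% | 4.9% | 84.7% → 88.4% | 3.7 |
| 27/29 | 3.6% | 4.9% | 83.5% → 87.8% | 4.3 |
| 30/29 | 3.6% | 4.7% | 86.6% → 88.6% | 2.0 |
| 29/30 | 3.6% | 4.7% | 87.6% → 89.3% | 1.7 |
| 30/32 | 4.0% | 4.9% | 88.1% → 90.4% | 2.3 |
| 32/30 | 4.0% | 4.9% | 90.4% → 91.1% | 0.7 |

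Boschloo's power was not below Fisher's in any split.

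**Step 3: what changes in practice.** At 28/28 the Boschloo cut-off is a Fisher P of about 0.080. Take 12 of 28 against 20 of 28 above the threshold, 32 of 56 in all. Fisher P = Σ C(28, x) C(28, 32 − x) / C(56, 32) over x ≤ 12 and x ≥ 20 = 0.058. Fisher does not reject; Boschloo does.

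**Step 4: other true effects.** With usual care at 0.40 and arms of 28/28, the gain is 0.8 points at a high-dose rate of 0.90, 2.4 at 0.85, 5.0 at 0.80, 8.0 at 0.75, 9.9 at 0.70 (50.8% → 60.7%) and 10.1 at 0.65. At 40% versus 70% the gain falls to 7.0 points at 31/31 (59.0% → 66.0%) and 1.1 at 29/30 (60.4% → 61.5%).

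**Step 5: safety outcomes, Fisher against Boschloo, 0% versus 20%.** At 28/28 power goes from 49.9% to 68.5%, a gain of 18.6 points. At 29/27 (81.8%) and 32/30 (87.7%) the two tests have identical power. The gain depends on the exact split.

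**The case against.** The strongest reply is that nothing here is wrong. The trial was sized for Fisher's test and is analysed with it, so the test's conservatism is already paid for in the 28 per arm. The 0.05 is an upper limit, and Fisher respects it. Replacing one valid, prespecified and adequately powered test with another is a preference about efficiency. All of that stands, and it is why this point is offered as an improvement and not as a defect.

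A reader might infer that the trial has no power to spare. The documents do not support that. With 59 to 62 children analysed, Fisher's power is about 87% at 40% versus 80% (86.6% at 30/29, 87.0% at 31/31). The 40% for usual care is also stated as a ceiling. At 30% versus 80% and 28/28, Fisher has 95.6% and Boschloo 97.5%.

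A reader might also take the loss to be 5 to 10 points in general, with about half of the error rate unspent. That holds only near 28/28, and the upper end needs a smaller effect than the one planned for. Permuted blocks of four within strata, together with missing samples, make exactly equal analysed arms uncertain.

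For the safety outcomes, the 18.6-point gain is measured against only one of the two tests that Secondary outcomes permits, so it cannot be presented as a loss built into the plan.

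Finally, the proposal concerns the unstratified comparison only. It does not address the stratified randomization or the conditional use of logistic regression. That is true, but it does not weaken the narrower point.

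**Conclusion.** The point holds as a cheap improvement. Fisher's test controls the error and delivers the stated 80% power. It also leaves part of the 0.05 unused: its maximum true error is about 2.5 to 3.0% with equal arms of 28 to 31, and about 3.4 to 4.0% when the arms differ by one or two. At the design proportions, Boschloo's test returns about 4 to 6 points with equal arms and about 1 to 4 with slightly unequal ones. Gains up to about 10 points require a smaller true effect and equal arms.

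These figures assume independent binomial outcomes, the probability-ordered two-sided Fisher P value, and an unstratified comparison. The unequal splits are illustrations; the final split is not known.

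**What to change.** Before unblinding, amend the Primary outcome section to say that the proportion with 25OHD below 50 nmol/L will be compared by Boschloo's unconditional exact test, two-sided at 0.05, with the two-sided Fisher P value reported as supportive. State how the Fisher P value is ordered and that the maximum is taken over the whole range of the common proportion, so that the result can be reproduced. Leave Sample size justification as it is; its figure becomes conservative.

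Using the same test for hypercalcemia and hypercalciuria is optional. It would settle the present choice between Fisher and chi-square, but the gain in power cannot be relied on.

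The cost is one sentence, a short validated routine and some unfamiliarity for readers. No more children are needed. Trial status reports 62% of the target enrolled at the time of writing, so the change could still have been made before the end of recruitment. If allocation has since been unblinded, keep Fisher's test as the primary analysis.

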### Randomization, blinding and stratification procedures

We will use a computer-generated randomization sequence. Only the CHEO pharmacy will have access to the randomization sequence and will be responsible for participant randomization and allocation. Only the pharmacist will know the identity of the study drug administered to specific patients. Given the expected recruitment (two to three per month) and potential impact of season on 25OHD, randomization will be performed in permuted blocks (four within each stratum). We will blind patients, families, investigators, hospital staff, and research personnel to treatment arm. Blinding was considered necessary to avoid (i) families altering the outpatient dose and (ii) a number of secondary outcome measures are that are potentially subjective (echocardiography, timing of extubation, need for fluids or catecholamine infusion). Within each age group, the two interventions will be indistinguishable (vial, volume, color, taste, consistency and smell).

Participants will be stratified into whether or not they are expected to receive at least 8 weeks of study drug prior to surgery. This stratification should guarantee that an equal number of CHD patients who will not receive 8 weeks of oral dosing end up in both the high and low dose arms. We will further stratify by age (under or over 1 year of age).

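### The primary Fisher test leaves out the factors used to stratify randomization, and adjustment waits on an undefined imbalance; a prespecified stratified test would gain some power at no cost in patients

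*Protocol article*

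**What the plan says.** All places are in the Protocol article.

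- **Randomization, blinding and stratification procedures:** "Participants will be stratified into whether or not they are expected to receive at least 8 weeks of study drug prior to surgery". A second factor is age, under or over 1 year. Blocks of four are used within each stratum.
- **Sample size justification:** the calculation uses the "two-sided Fisher’s exact test and the significance level of the test was targeted at 0.05". It assumes that "no more than 40 % of the usual care arm will have postoperative 25OHD levels above 50 nmol/L" and "we anticipate that 80 % of the high dose arm will have postoperative levels above 50 nmol/L", so that "group sample sizes of 28 in both treatment arms will be required to achieve 80 % power".
- **Primary outcome:** differences in the proportion deficient "between the treatment groups will be evaluated using the Fisher’s exact test". Then: "Logistic regression analysis will be used if important variables are unevenly distributed between groups".
- **Secondary outcomes:** the same conditional rule is repeated, with weight as the one example of an important variable.
- **Subgroup analysis:** children operated on within two months of birth or diagnosis are also analysed separately. The proportion above 50 nmol/L is expected to stay low there even on high dose, and a figure of 25% is given.
- **Duration of study drug:** 75 to 80% of patients are expected to receive study drug for more than 2 months.

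**The concern.** The design treats expected duration as important enough to stratify on, and the subgroup section treats it as strongly prognostic. The primary test then ignores it. Balancing a prognostic factor by design and leaving it out of the analysis makes the test conservative: the test allows for between-stratum variation that the randomization has already removed from the comparison.

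The conditional regression rule does not repair this. Blocking within strata makes visible imbalance on the stratification factors unlikely, so the rule would rarely bring in the covariates that matter most. If it fires on some other variable, the supporting analysis is a logistic model with a conditional odds ratio, chosen by a judgement that the text does not define. At stake are some power in a 62-patient trial and a clear statement of which adjusted result counts.

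**Working it through.** **1. The plan's own figure.** Inputs from the sample size section: p1 = 0.40, p2 = 0.80, d = 0.40, two-sided alpha 0.05, power 80%. With mean proportion 0.60:

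n0 = [1.960·√(2·0.60·0.40) + 0.842·√(0.40·0.60 + 0.80·0.20)]² / 0.40² = (1.358 + 0.532)² / 0.16 = 22.3

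With continuity correction: n = (22.3/4)·[1 + √(1 + 4/(22.3·0.40))]² = 27.1, so 28 per arm. Exact power of the two-sided Fisher test, summing binomial probabilities over all tables, is 79.9% at 26, 80.2% at 27 and 82.3% at 28 per arm. The stated 28 reproduces.

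**2. Tests compared.** All use 28 per arm: unstratified Fisher, unstratified chi-square, exact stratified (the conditional test from the summed within-stratum hypergeometric distributions), and CMH without continuity correction. Fisher against exact stratified, and chi-square against CMH, are the like-for-like pairs.

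**3. Stratum inputs.** The short stratum is 20 to 25% of 28, so 6 or 7 per arm. Short-stratum success on high dose is 25%, from the subgroup section. Its wording (an estimated prevalence) is ambiguous, and I read it as the proportion above 50 nmol/L. Short-stratum success on usual care is not in the document; I assume 10 to 15%. For the long stratum I apply the plan's 80% v 40%, also an assumption. The lower rows keep 80% v 40% overall, with stratum rates that I assumed.

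**4. Power**, by exact enumeration with two duration strata:

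| Scenario (high dose v usual care) | Fisher | Chi-square | Exact stratified | CMH | Fisher to exact stratified | Chi-square to CMH |
|---|---|---|---|---|---|---|
| Long 80 v 40; short (6/arm) 25 v 10 | 65.3% | 75.6% | 73.9% | 81.0% | +8.6 | +5.4 |
| Long 80 v 40; short (6/arm) 25 v 15 | 61.8% | 72.5% | 69.8% | 77.4% | +8.0 | +5.0 |
| Long 80 v 40; short (7/arm) 25 v 10 | 62.5% | 73.2% | 71.2% | 80.2% | +8.7 | +7.0 |
| Long 80 v 40; short (7/arm) 25 v 15 | 58.2% | 69.4% | 66.2% | 75.9% | +8.0 | +6.5 |
| Overall kept, mild strata: 86.7 v 46.7; short 60 v 20 | 83.1% | 89.0% | 85.1% | 90.4% | +2.0 | +1.3 |
| Overall kept, weak strata: 83.3 v 43.3; short 70 v 30 | 82.5% | 88.4% | 82.3% | 88.3% | −0.1 | −0.1 |
| Strata not prognostic: 80 v 40 in both | 82.3% | 88.2% | 81.4% | 87.7% | −0.9 | −0.5 |

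In the first row CMH exceeds Fisher by 81.0 − 65.3 = 15.7 points. Of these, 75.6 − 65.3 = 10.3 come from leaving the exact test and 81.0 − 75.6 = 5.4 from stratifying.

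**5. Four strata.** A simulation of 20,000 trials with both factors (11, 11, 4 and 2 per arm; 25% v 10% in the short strata) gave Fisher 65.4%, exact stratified 73.4% and CMH 81.7%. Sparse strata do not remove the gain.

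**6. Type I error.** With no treatment effect and success rates (long, short) of 40/40, 46.7/20, 60/10 and 80/25%: Fisher 1.1 to 2.6%, exact stratified 2.2 to 2.5%, CMH 4.5 to 5.1%.

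**7. The trigger.** In simulations of 6,000 trials with one continuous prognostic covariate (assumed log-odds 1 per SD), power was 65.7% for Fisher. It was 66.5% or 69.0% when adjustment was triggered by a baseline p below 0.05 or 0.20, and 80.7% with adjustment always applied. Part of that last gain is again the move away from Fisher: with a covariate of no prognostic value, power was 82.4% for Fisher and 87.2% for logistic regression. Over null settings with covariate log-odds of 0, 1 and 2, the triggered rule had type I error of 2.1 to 2.8%; taking the smaller of the two p-values gave 4.3 to 6.0%.

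**The case against.** The strongest reply is that nothing here is invalid. Fisher's test controls type I error, the sample size was computed for that same test, and 28 per arm delivers the stated power at the stated rates. The gain from stratifying rests on stratum rates that the protocol mostly does not give. A separate analysis of early-surgery children is planned, so the factor is not forgotten. The regression sentence can be read as a supplementary analysis, and a list of covariates is commonly left to an analysis plan. All of this stands, and it limits the point to efficiency and prespecification. It does not answer the fact that the text fixes a primary test without the randomization factors and an adjustment rule unlikely to bring them in.

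Some stronger readings are tempting but unsupported:

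- **That stratifying yields the whole Fisher-to-CMH difference of about 16 points.** About 10 of those are available from an unstratified chi-square test.
- **That the sample size is wrong.** The lower Fisher power of 58 to 65% arises because a poorly responding short stratum dilutes the overall contrast to about 66 to 68% v 33 to 35%. That is a question about planning rates, separate from the choice of test.
- **That baseline significance tests drive the switch to regression.** The descriptive section says "Statistically significant differences will be determined using Chi-square" and other tests, but no sentence ties them to the regression rule or says that the choice is made from unblinded data.
- **That the trigger seriously inflates type I error.** In the check it stayed below 3%. Only picking the smaller p-value reached 6.0%.

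**Conclusion.** The point holds as a low-cost improvement. The primary analysis does not reflect the randomization, and the conditional adjustment rule is loosely fixed. If short-duration children make up 20 to 25% of patients and respond as the subgroup section suggests, stratifying adds about 5 to 9 points of power with the same 56 evaluable patients. This rests on reading the 25% as high-dose success, on usual-care success of 10 to 15% in that stratum, and on 80% v 40% in the long stratum. With mild or non-prognostic strata the difference is about 0 to 2 points, and the exact stratified test can lose up to 1 point. The further gain with CMH comes from moving from a test of size about 1 to 3% to one near 5%, and gives up the guaranteed size of an exact test. The stated sample size is not in error.

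**What to change.** - **Primary test.** Prespecify an exact stratified (conditional) test on the randomization strata, or CMH if a size near 5% without an exact guarantee is acceptable. Report the Mantel-Haenszel risk difference with its 95% CI.
- **Strata.** Keep all strata as randomized, or state in advance that only the duration factor is used. Do not drop a factor after seeing the counts, which would be another data-dependent choice. It is also unnecessary: a stratum with one arm empty, or with the same outcome in everyone, contributes nothing to the test.
- **Sensitivity.** Keep the unstratified Fisher test.
- **Adjustment.** Replace the imbalance trigger, for primary and secondary outcomes alike, by prespecified adjustment for expected duration and age, and put the same two factors in the secondary regression models.

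The cost is analysis wording only. The strata are set at randomization, so no extra patients, visits or data are needed. The change should be fixed before unblinding.
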